### Randomization

The participants will be randomly assigned to two groups after the initial examination and upon completing the baseline data form. Random sequencing will be done in blocks of 4 using the randomization website at http://www.jerrydallal.com/random/permute.htm. The ratio of assignment to each arm will be 1:1 and each group will have 66 individuals.

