## Intervention

### Intervention and control groups

In addition to the usual care, the participants of the intervention group will receive the educational, supportive mobile application-based intervention (Additional file 2). The participants will have these applications for 6 months and the aforementioned measurements will be registered in it. Reminders for dose and time of drug intake, date of clinical visit, and other reminders will be activated. The users will be provided with the scientific information and skills required to identify the disease and its methods of control by the mobile application.

The participants in the comparison arm will receive the usual standard care based on the Joint National Committee (JNC) guideline. The usual care includes, measuring the patient’s BP, necessary assessments based on the patient’s history and circumstances, the specialist physician’s judgment, medication prescription, and other medical measures. The number of appointments and assessments in each group will be the same. The intervention and control participants’ appointment days will differ and the members of one group will not be in touch with those of the other.

The BPMAP application contains educational content that is meant to raise the level of knowledge in hypertensive patients regarding its complications and methods of control. Moreover, it contains supportive measures such as important reminders for time of drug use, smoking cessation, and weight loss.

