### Sample size

The sample size is 120 (60 persons in each group) with a power of 80 % to detect a minimum difference of five scores (a mean of 40 and 45 in the control and intervention groups and a standard deviation of 10). Based on the Hill-Bone High Blood Pressure Therapy Compliance Scale [9], the mean difference was calculated with the two-tailed test at a significance level of 5 %. Bearing in mind the possibility of sample loss, 10 % was added to the sample size and 132 persons were estimated.

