### Follow-up

The participants will be examined seven times at 2-week intervals (Table 1). In the first visit, after ensuring the participant’s inclination to participate in the study and after the informed consent form is completed, the baseline data questionnaire will be completed by the researcher. Clinical measurements, such as systolic and diastolic BP, waist circumference and hip circumference, BMI, and biochemical measurements, such as LDL, HDL, and total cholesterol levels, will be performed.

**Table 1 Tab1:** Steps taken in each visit

	Study period										
	Enrollment	Allocation	Post allocation								Close-out
Week	−1 to 0	0 ± 2 days	2 ± 2 days	4 ± 2 days	6 ± 2 days	8 ± 2 days					24 ± 2 days
Time point	1^st^ visit	2^nd^ visit	3^rd^ visit	4^th^ visit	5^th^ visit	6^th^ visit					7^th^ visit
Enrollment:	×										
Eligibility screen	×										
Informed consent	×										
Allocation	×										
Intervention		×	×	×	×	×	×	×	×	×	×
Assessment	×					×					×
Baseline variables	×					×					×
Measuring adherence to treatment	×					×					×
Measuring adherence to the diet	×					×					×
Evaluating the predisposing, enabling, and reinforcing factors of adherence	×					×					×
Measurement of systolic and diastolic BP, waist circumference, and BMI	×	×	×	×	×	×	×	×	×	×	×
Evaluating the regular monitoring of BP by the mobile application	×	×	×	×	×	×	×	×	×	×	×
Evaluating the usability of the software						×					×
Evaluating the level of satisfaction of the software/application						×					×

*BMI* Body Mass Index, *BP* blood pressure

The 2nd visit will be made a week after the first. The application will be installed on the cell phones of the intervention group’s patients and its operation will be taught to them. Any problems that arise will be dealt with accordingly. Moreover, the sphygmomanometer used by the patient at home will be evaluated for its precision and sensitivity (calibration). In order to ensure that the patients measure their BP correctly at home, the methods applied by them will be controlled, and if faulty, corrected. Clinical measurements and usual care will be performed. The usual care includes history taking, BP measurement, and diagnostic and therapeutic measures based on the JNC guideline on high blood pressure.

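### A single published block size of 4, with arms visible at one centre, lets a recruiter who tracks allocations foresee up to one third of them

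*Protocol article*

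**What the plan says.** The Randomization section fixes the method: "Random sequencing will be done in blocks of 4 using the randomization website". It continues: "The ratio of assignment to each arm will be 1:1 and each group will have 66 individuals". It mentions neither stratification nor a varying block size. Assignment follows the initial examination and the baseline form. Study setting names one clinic as the source of all patients, so one list covers the whole trial. Trial status says that recruitment was under way when the article appeared, so the block size was public while patients were still being enrolled.

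Three features make the arm visible to the team:
- At the second visit (Follow-up), "The application will be installed on the cell phones of the intervention group" patients, who are then taught to use it.
- The comparison arm receives usual care, with no sham application (Intervention and control groups).
- The same section says that the two arms' "appointment days will differ and the members of one group will not be in touch with those of the other".

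The article does not use the term open-label, but these features amount to it as far as the research team is concerned.

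**The concern.** In a permuted block of constant size, the later places are partly or wholly determined by the earlier ones. When staff can see past allocations and know the block size, they can work out some future ones. Concealing the list does not prevent this, because the deduction uses only what has already happened.

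Randomising after the baseline form does not prevent it either. The anticipation can act earlier, on who is approached, when, and who is judged eligible. Some eligibility items under Participants involve judgement: adequate literacy, ability to use a smartphone and willingness to take part. These plausibly relate to motivation, and motivation plausibly affects the self-reported compliance score on which the trial was sized. If enrolment were steered in this way, the arms would differ at entry. The analysis of covariance on baseline score and possible confounders could correct only the part of that difference that the measured covariates capture.

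**Working it through.** **Inputs from the protocol article**
- Block size 4, ratio 1:1, 66 per arm (Randomization).
- Total: "10 % was added to the sample size and 132 persons were estimated" (Sample size).
- "The sample size is 120 (60 persons in each group) with a power of 80" %, with "a mean of 40 and 45 in the control and intervention groups and a standard deviation of 10" (Sample size). From these come SD = 10, 60 per arm and a target difference of 45 − 40 = 5 points.
- Two-sided 5% test (Sample size).

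**The plan's own figure.** 120 × 1.10 = 132. Then 132 / 4 = 33 complete blocks, each with 2 per arm, so 66 + 66. This agrees with the text.

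**Allocations known for certain.** There are 6 equally likely orders in a 1:1 block of 4.
- Places 1 and 2 are never forced.
- Place 3 is forced when the first two match, which happens in 2 of 6 orders, or 1/3.
- Place 4 is always forced.
- Forced per block = 1/3 + 1 = 4/3. Share = (4/3) / 4 = 1/3 = 33.3%.
- Over 33 blocks: 33 × 4/3 = 44 expected, SD = sqrt(33 × 1/3 × 2/3) = 2.7.

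**Best guess** (always name the arm with fewer allocations so far in the block). The probabilities of being right at places 1 to 4 are 1/2, 2/3, 2/3 and 1. The mean is 17/24 = 70.8%, against 50% under simple randomisation.

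**If the latest allocation is not yet visible.** Place 4 is then known only when places 1 and 2 match, and no other place is known: (1/3) / 4 = 8.3% certain. Best guess = (1/2 + 1/2 + 2/3 + 2/3) / 4 = 58.3%. If the latest two are not visible, no place is certain.

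**Illustration of consequence.** The documents give no steering figure, so this is an assumption shown over a range. Let s be the prognostic difference between arms, in points, among the certain allocations only.
- Bias = s × 1/3.
- Unadjusted SE = 10 × sqrt(2/60) = 1.83.
- Type I error = P(|Z + bias/SE| > 1.96).

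| s (points) | bias (points) | type I error |
|---|---|---|
| 1 | 0.33 | about 5.4% |
| 3 | 1.0 | about 8.5% |
| 5 | 1.67 | about 15.0% |

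Analysis of covariance would change these figures. It alters the SE and removes whatever part of s the baseline score carries.

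**Alternative block schemes** (exact enumeration for fixed sizes; simulation for varied sizes, 400 runs of 132 patients, with a recruiter who knows the set of sizes but not their order)

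| scheme | certain | best guess |
|---|---|---|
| fixed 4 | 33.3% | 70.8% |
| fixed 6 | 25% | 68.3% |
| fixed 8 | 20% | 66.6% |
| random 4/6 | about 5% | about 69% |
| random 4/6/8 | about 2% | about 68% |

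**The case against.** No passage contradicts another here. Blocks of 4 are a design choice, and the criticism concerns risk. The strongest objections are these.

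**One third is a ceiling.** It requires one person to know every earlier allocation in order, and the block starts, before approaching the next patient. The article names different roles: a physician judges eligibility, the researcher completes the questionnaire, and the research team sets up the app. It does not say that whoever approaches patients follows the running order. The app is installed a week after the first visit, and Table 1 places allocation under the second visit in its column heading but marks it at the first visit in its row. If the arm becomes visible only at the second visit, patients enrolled in between are unknown to staff and the share drops, to 8.3% with one unknown. This stands, and the one third must be read as an upper figure.

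**The remedy is partial.** Suppose steering follows best guesses instead of certainties, so that bias = s × (2p − 1), where p is the best-guess rate. With s = 3, fixed blocks of 4 give 3 × (2 × 0.708 − 1) = 1.25 points and about 10.5% type I error. Random 4/6/8 blocks, with p about 0.679, give about 1.07 points and 9.0%. On that measure about 86% of the bias remains (1.07 / 1.25). This also stands. The gain is in removing certainty, which is what would make deliberate deferral or refusal dependable.

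**Custody of the list.** A reader might infer from the article's silence that nobody independent holds the list. The text does not support this: a condensed article may leave custody and concealment to the full protocol, and no fault is charged for it. The point does not need it, because forced places can be deduced from past allocations even when the list is perfectly concealed.

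**Conclusion.** The point holds as a modest one, worth considering and not essential. A constant, published block size of 4, on one list at one centre with visible arms, allows a recruiter who tracks allocations and block starts to know up to 33.3% of them (44 of 132 expected) and to guess 70.8%. Both figures are exact under that assumption and lower if recent allocations are not yet visible.

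Two stronger readings should be resisted. One is that selective enrolment is happening or is likely: the documents show the opportunity and nothing about conduct. The other is that the trial's type I error is some stated value above 5%. The 5.4% to 15.0% range rests entirely on assumed steering of 1 to 5 points and an unadjusted SE, and it shows sensitivity only.

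**What to change.** Generate the remaining part of the sequence with block sizes varied at random, for example 4, 6 and 8, keep the 1:1 ratio, and do not disclose the sizes to recruiting staff. Start the new list at the end of a completed block of 4. Amend the Randomization section to say that block sizes vary, without listing them in material that recruiters see, and to say about 66 per arm where it now promises exactly 66.

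The cost is regenerating the list and a short amendment. The arms may finish unequal by at most 4 patients (half the largest block), which is negligible for power. Because recruitment had begun, only patients not yet randomised benefit.

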### Follow-up

The participants will be examined seven times at 2-week intervals (Table 1). In the first visit, after ensuring the participant’s inclination to participate in the study and after the informed consent form is completed, the baseline data questionnaire will be completed by the researcher. Clinical measurements, such as systolic and diastolic BP, waist circumference and hip circumference, BMI, and biochemical measurements, such as LDL, HDL, and total cholesterol levels, will be performed.

**Table 1 Tab1:** Steps taken in each visit

	Study period										
	Enrollment	Allocation	Post allocation								Close-out
Week	−1 to 0	0 ± 2 days	2 ± 2 days	4 ± 2 days	6 ± 2 days	8 ± 2 days					24 ± 2 days
Time point	1^st^ visit	2^nd^ visit	3^rd^ visit	4^th^ visit	5^th^ visit	6^th^ visit					7^th^ visit
Enrollment:	×										
Eligibility screen	×										
Informed consent	×										
Allocation	×										
Intervention		×	×	×	×	×	×	×	×	×	×
Assessment	×					×					×
Baseline variables	×					×					×
Measuring adherence to treatment	×					×					×
Measuring adherence to the diet	×					×					×
Evaluating the predisposing, enabling, and reinforcing factors of adherence	×					×					×
Measurement of systolic and diastolic BP, waist circumference, and BMI	×	×	×	×	×	×	×	×	×	×	×
Evaluating the regular monitoring of BP by the mobile application	×	×	×	×	×	×	×	×	×	×	×
Evaluating the usability of the software						×					×
Evaluating the level of satisfaction of the software/application						×					×

*BMI* Body Mass Index, *BP* blood pressure

The 2nd visit will be made a week after the first. The application will be installed on the cell phones of the intervention group’s patients and its operation will be taught to them. Any problems that arise will be dealt with accordingly. Moreover, the sphygmomanometer used by the patient at home will be evaluated for its precision and sensitivity (calibration). In order to ensure that the patients measure their BP correctly at home, the methods applied by them will be controlled, and if faulty, corrected. Clinical measurements and usual care will be performed. The usual care includes history taking, BP measurement, and diagnostic and therapeutic measures based on the JNC guideline on high blood pressure.

From the 2nd visit onward (up to the 6th visit) patients will be visited every 2 weeks. In each visit the patient’s BP, weight and waist circumference will be measured, and standard antihypertensive therapeutic measures – based on the JNC guideline – will be taken.

On the 6th visit, in addition to the assessments made throughout the 2^nd^ to 5^th^ visits, the baseline data questionnaire will be completed for the patients as well.

On the 7th visit, which will be conducted 16 weeks after the 6^th^ visit, the baseline data questionnaire as well as clinical assessments will be evaluated.

On the 6th and 7th visits, the intervention group’s patients will be asked whether they are familiar with another person involved in this study. If the response is positive they will be asked further questions and the data will be included in the analysis. This question will be included to take into account the possibility of contact between the participants of the control and intervention groups.

### Withdrawal criteria

The participant will be excluded from the study if any of the following are seen during the study:Lack of registration of data in the application for more than a weekLack of interest in continuing to participate in the studyNonattendance for two consecutive visitsChange in dose and type of antihypertensive medicationHospital admission due to CVDEmigration from TehranDeath

### Data management

Patient information will be collected from two sources: (1) digital data collected on the server and (2) a questionnaire assessing risk factors and adherence to treatment, which is on paper and which will be completed by the researcher. The entire data will be prepared from a SPSS database based on a pre-defined data dictionary. To ensure the validity of data, data entry will take place through double entry.

## Statistical methods

The qualitative findings of the study will be described using frequency and percentage frequency, and the quantitative findings will be described using mean and standard deviation. To analyze the effectiveness of the main outcome variable of the study, we will use analysis of covariance (comparison of mean changes in score of the adjusted questionnaire – based on the baseline score at the beginning of the study and other possible confounding factors) at a confidence interval of 95 %. This approach will be repeated for all the quantitative variables.

The remaining qualitative variables of the study will be compared by the chi-squared test between the two groups. The main approach of the study will be intention-to-treat. The final results will be analyzed per protocol. Lost data will be replaced through multiple imputation techniques.

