#### Adherence to antihypertensive medication use

This will be assessed with the Hill-Bone High Blood Pressure Therapy Compliance Scale, which includes 14 items, at the initial and final assessments [9–11]. Individuals will score from 14 to 56. An increase exceeding 20 % of the Compliance Scale score is considered effective.

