#### Regular BP monitoring

BP can be regularly monitored by regularly measuring and saving the relevant data in the mobile app. For every timely registration a score will be awarded. This part of the study is 60 days long. The participants will be asked to measure and register their BP once every other day. A score of 25 and higher will be considered appropriate.

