#### Smoking cessation

This will be evaluated through a couple of questions in the questionnaire, at the baseline assessment and at the 8^th^ and 24^th^ weeks.

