#### Predisposing factors, enabling factors and reinforcing factors of adherence

Some of the questions of the questionnaire assess these factors. These measurements are performed at the baseline assessment and at the 8^th^ and 24^th^ weeks. A 20 % increase in score is considered desirable.

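### Qualitative outcomes get an unadjusted chi-squared test although a baseline value is collected for at least one of them (smoking), which gives up power and leaves chance imbalance in the estimate

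*Protocol article*

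**What the plan says.** The protocol article, under Statistical methods, sets out two rules.

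- **Quantitative outcomes.** "To analyze the effectiveness of the main outcome variable of the study, we will use analysis of covariance", with the baseline score and other possible confounders as covariates. The scope is then widened: "This approach will be repeated for all the quantitative variables".
- **Qualitative outcomes.** "The remaining qualitative variables of the study will be compared by the chi-squared test between the two groups". No covariate or stratification factor is mentioned.

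Smoking cessation appears in the list under Primary outcomes/behavioral. Its own subsection says: "This will be evaluated through a couple of questions in the questionnaire, at the baseline assessment", and adds weeks 8 and 24. Under Randomization, allocation is 1:1 in blocks of 4, and no stratification factor is stated.

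One outcome with a cut-off is different in kind. Regular BP monitoring is scored from entries made in the app over 60 days: "A score of 25 and higher will be considered appropriate".

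**The concern.** The plan accepts baseline adjustment for one type of data and drops it for the other without giving a reason. The argument for adjustment does not depend on the type of data. If baseline status predicts follow-up status, using it removes outcome variation that has nothing to do with treatment, and it corrects for whatever imbalance the randomization happened to leave.

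Two things are at stake for a categorical outcome with a recorded baseline. The first is power, in a trial of about 60 evaluable patients per arm. The second is the reading of the result if the arms differ at baseline by chance: that difference passes into an unadjusted comparison, and a reader cannot separate it from the effect of the app.

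**Working it through.** **Which outcomes the sentence reaches**

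| Outcome | Baseline collected? | Planned analysis | Affected? |
|---|---|---|---|
| Hill-Bone adherence score | Yes | ANCOVA | No |
| BP, lipids, BMI, waist circumference | Yes | ANCOVA | No |
| Smoking status | Yes | Chi-squared | Yes |
| App-based BP-monitoring cut-off | No usable one before installation | Chi-squared if analysed as a cut-off | No |

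Smoking is therefore the one clear case.

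**The plan's own power figure.** Sample size states 80% power at 60 per arm for a difference of 5 with SD 10. The normal approximation gives Φ(5/(10·√(2/60)) − 1.96) = Φ(0.78) = 78%. This concerns the continuous adherence score. No power figure or rate is given for any categorical outcome. Only the 60 per arm is used below.

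**Inputs.** From the protocol: 60 per arm, two-sided 5%. Assumed: 40% prevalence at baseline and at control follow-up; an effect of 0.6 on a unit-variance latent normal scale; latent correlation between baseline and follow-up of 0.3, 0.5, 0.7 or 0.85.

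**Chi-squared power by formula.**
- The threshold for 40% is 0.253, so the intervention rate is 1 − Φ(0.253 − 0.6) = 63.6%, a difference of 0.236.
- Pooled rate 0.518: null SE = √(2 × 0.518 × 0.482/60) = 0.0912.
- Alternative SE = √((0.4 × 0.6 + 0.636 × 0.364)/60) = 0.0887.
- Power ≈ Φ((0.236 − 1.96 × 0.0912)/0.0887) = Φ(0.64) = 74%.

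The correlation does not enter this formula, so chi-squared power is the same at every strength of baseline link.

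**Simulation**, 20,000 trials per setting (Monte Carlo SE about 0.3 points):

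| Latent correlation | Chi-squared | Baseline-stratified test | Gain (points) |
|---|---|---|---|
| 0.3 | 75% | 75% | 0 |
| 0.5 | 75% | 78% | 3 |
| 0.7 | 75% | 84% | 9 |
| 0.85 | 75% | 91% | 15 to 16 |

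Type I error is about 5% for both tests.

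**A second model.** This used 40,000 trials per setting, 50% baseline prevalence and a Cochran-Mantel-Haenszel test. The effect differs between rows, so compare only within a row.

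| Control follow-up rates by baseline status | Chi-squared | Stratified |
|---|---|---|
| 40% / 60% | 74.5% | 75.7% |
| 30% / 70% | 66.2% | 72.6% |
| 20% / 80% | 54.6% | 70.0% |
| 10% / 90% | 33.1% | 61.8% |

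The direction is the same: about 1 point with a weak link, rising to 29 at the extreme.

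**Chance imbalance.** At 40% prevalence the between-arm difference at baseline has SD √(2 × 0.4 × 0.6/60) = 0.089, about 9 percentage points. In simulations at 60 per arm, a baseline difference of 10 points or more arose in 21% to 32% of trials (prevalence 20% to 50%). With no true effect, the chi-squared false-positive rate in those trials was about 6% with a weak link (40%/60%) and 16% to 20% with a very strong one (5%/90%). The stratified test stayed near 5%. Over all trials chi-squared also stayed near 5%.

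**The case against.** The strongest reply is that an unadjusted chi-squared test is a valid comparison in a 1:1 randomized trial. Chance imbalance is already paid for in its 5% error rate, so this is a choice between two valid tests. That stands. A reader might infer that the planned test inflates false positives, and it does not. The excess appears only among trials that happen to be imbalanced.

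The second reply is that the scope is narrow. That also stands. It would be wrong to infer that power is lost across the primary outcomes. The score that sizes the trial and the other quantitative measures are already adjusted, and the BP-monitoring cut-off has nothing to adjust for. The 20% rises in questionnaire scores have baseline built into their definition, and the protocol does not say that they will be tested by chi-squared.

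The third reply is that cessation can be read as quitting among baseline smokers. On that reading baseline smoking status is constant and adjustment for it falls away. A reader might instead infer that the plan pools never-smokers with quitters, but the text does not say so. The denominator for cessation, the handling of sparse cells, and the effect measure with its interval are details that an article may leave to the full plan. Their absence here is not held against the protocol.

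The fourth reply is that the rates are assumed. They are, and with a weak baseline link the gain is nil. What survives is that the protocol does not leave the method open: it names an unadjusted test beside an adjusted one and leaves a collected baseline value unused.

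**Conclusion.** The point holds as a matter of efficiency and precision, not validity. For smoking status, and for any other qualitative outcome with a baseline measurement, the planned test gives up power and leaves chance baseline imbalance in the estimate. Under the main assumptions (60 per arm, 40% prevalence, latent shift 0.6) the loss runs from nil at a latent correlation of 0.3 to about 15 points at 0.85. The second set of assumed rates gives a wider range at its extreme. Smoking status over 24 weeks plausibly has a strong link to baseline, but the protocol gives no figure for this. Severity is minor to modest: the main outcome is unaffected and overall type I error is kept.

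**What to change.** Replace the chi-squared sentence. For each qualitative outcome with a baseline measurement, compare the arms by logistic regression with arm and the baseline value of the same variable, or by a Cochran-Mantel-Haenszel test stratified on that value. Keep the chi-squared test as a sensitivity analysis. State that outcomes without a usable baseline, such as the app-based BP-monitoring cut-off, stay unadjusted, as does cessation if it is analysed among baseline smokers only.

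The cost is a change of wording and slightly more analysis. No new data, visits or patients are needed. Trial status says recruitment is under way, so the change can be fixed before outcomes are compared and will not look like a choice made after the event.

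### Statistical methods names intention-to-treat as the main approach and per protocol for the final results, without ranking them or defining a per-protocol set, so either could be reported as the trial's answer

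*Protocol article*

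**What the plan says.** Three statements in the Statistical methods section of the protocol article bear on this.

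- The efficacy model: "To analyze the effectiveness of the main outcome variable of the study, we will use analysis of covariance". It compares score changes adjusted for baseline and possible confounders. No analysis set is named.
- The analysis sets, in two adjacent sentences: "The main approach of the study will be intention-to-treat. The final results will be analyzed per protocol". The second is not labelled secondary, supportive or sensitivity.
- Missing data: "Lost data will be replaced through multiple imputation techniques". This is tied to neither analysis.

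The Withdrawal criteria section adds: "The participant will be excluded from the study if any of the following are seen during the study". Seven criteria follow: no app registration for more than a week, loss of interest, missing two consecutive visits, a change in antihypertensive medication, hospital admission for cardiovascular disease, leaving Tehran, and death. The Intervention and control groups section gives the app to one arm: in addition to usual care, "the participants of the intervention group will receive the educational, supportive mobile application-based intervention".

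No other part of the article mentions intention-to-treat or a per-protocol analysis.

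**The concern.** A plan should say which analysis gives the result. Here one sentence gives intention-to-treat the leading role and the next assigns the final results to per protocol. The two analyses answer different questions and can give different answers. If the ranking stays open, it can be settled once both results are seen.

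The choice matters more than usual in this trial. The outcome behind the sample size is a treatment-adherence score, and a per-protocol set usually keeps people who engaged with the intervention. Engagement with an adherence app and a good adherence score are likely to go together. Comparing engaged app users with controls who were not filtered on engagement gives up the protection of randomisation.

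**Working it through.** The main check is a reading of the text. The arithmetic only shows how much the choice of set could matter.

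**Step 1: is there a ranking?** Intention-to-treat is called the main approach. Per protocol is attached to the final results. Neither the model statement nor the imputation statement refers to either set, and no other section settles the matter. The precedence is unresolved in the stated text.

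**Step 2: what would the per-protocol set be?** The article does not define one. The withdrawal criteria are the only list of exclusions after enrolment, so they are the natural candidate. This is an inference.

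**Step 3: do those criteria act equally in both arms?** Six of the seven can occur in either arm. The app-registration criterion cannot: under Follow-up, the app is installed only on the phones of intervention patients. Applied literally to controls, the criterion would exclude all of them, so the only workable reading is that it acts in the app arm alone. It selects on engagement after randomisation.

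**Step 4: illustration of size, with no true effect.**

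Inputs:
- SD = 10 and planned difference = 5 (Sample size section).
- q, the fraction of the app arm excluded: 20% to 40% (assumption).
- ρ, the correlation between engagement and adherence score: 0.3 to 0.5 (assumption).
- The least engaged fraction q is excluded, engagement and score are jointly normal, and no comparable selection occurs among controls (assumptions).

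Formula: spurious difference = SD × ρ × φ(z_q) / (1 − q), where z_q is the q-quantile of the standard normal distribution and φ is its density.

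- q = 0.20: z = −0.842, φ = 0.280, and 0.280 / 0.80 = 0.350
- q = 0.40: z = −0.253, φ = 0.386, and 0.386 / 0.60 = 0.644

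| q | ρ = 0.3 | ρ = 0.5 |
|---|---|---|
| 20% | 10 × 0.3 × 0.350 = 1.05 | 10 × 0.5 × 0.350 = 1.75 |
| 40% | 10 × 0.3 × 0.644 = 1.93 | 10 × 0.5 × 0.644 = 3.22 |

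The range is about 1 to 3 points, or 1.05 / 5 = 21% to 3.22 / 5 = 64% of the planned difference.

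**Step 5: allow for the planned ANCOVA.** Suppose selection acts through the part of the score not explained by baseline, and the baseline–follow-up correlation is 0.5 to 0.7 (assumption). The residual SD is 10 × √(1 − 0.5²) = 8.66 or 10 × √(1 − 0.7²) = 7.14. The smallest value becomes 0.714 × 1.05 = 0.75 and the largest 0.866 × 3.22 = 2.79. Adjustment reduces the distortion without removing it.

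**The case against.** The strongest defence is that the article does give a rank: intention-to-treat is the main approach, and the per-protocol sentence may be a badly worded promise of an additional analysis at study end. That pairing is ordinary and may well be what was meant. It stands as a possible intention, but the sentence does not say so, and final results is an odd label for a supporting analysis. Per protocol could also mean as the protocol prescribes, but directly after intention-to-treat it reads as the technical term. An unseen analysis plan does not dispose of the point, because the analysis set is not left out of the article. It is stated in two ways that do not fit together.

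Three stronger readings are tempting, and the documents do not support them.

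- **That the per-protocol analysis definitely supplies the trial's result, and a national roll-out would rest on it.** This gives no weight to the word main. The abstract says only that the app may be extended if its impact is proven.
- **That the per-protocol comparison sets adherent app users against unselected controls.** The set is undefined, and six of the seven criteria also select among controls. The net bias of the whole list is not established. A direction can be argued only for the app-registration criterion.
- **That power falls from 80% to about 72%.** The lower figure takes 53 per arm, which assumes 20% excluded from both arms, whereas the bias argument puts exclusions mainly in one. With 20% excluded from the app arm alone (66 against about 53), power is about 77%. The 80% is also not reached at the planned 60 per arm, where power is about 77.5% to 78%; that is a separate matter. The comparison should not be used.

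**Conclusion.** The point holds as a defect in stated precedence: two analysis approaches stand side by side with no order between them and no definition of the second, so either could be reported as the answer. This conclusion rests on the text alone and needs no figure.

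The likely direction of harm is conditional. If the per-protocol set follows the withdrawal criteria, the app-registration criterion removes participants from one arm only, by engagement, and would probably favour the app on an adherence score. The size, about 1 to 3 points unadjusted and about 0.7 to 2.8 after baseline adjustment, is an illustration. The excluded fraction and both correlations are assumed, and only the SD of 10 and the 5-point difference come from the protocol.

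The ambiguity also extends to the withdrawal rule. It removes people from the study altogether, so it could deplete the intention-to-treat set as well unless the two sections are reconciled. The point should be settled before any outcome is analysed, because it decides which estimate is the trial result.

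**What to change.** In Statistical methods, replace the per-protocol sentence with wording to this effect: the primary and final conclusion rests on the intention-to-treat analysis of all randomised participants in their assigned arm, with multiple imputation of missing outcomes; a per-protocol analysis, in a set defined before the data are examined, is secondary only.

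Reconcile the Withdrawal criteria section with this. State that participants who meet a criterion stay in the intention-to-treat analysis set and that any outcome data available for them are used. Without this second change, the first would leave open whether withdrawn participants are analysed at all. The change concerns who is analysed; it takes no position on the clinical criteria themselves.

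The cost is a few sentences in two sections and a short definition of the per-protocol set. No added recruitment or measurement is needed, and the article reports that the trial is still recruiting.
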